### Randomization and blinding

Eligible patients will be randomly allocated to one of two experimental groups (see “Groups and treatments” section below). A stratified block randomization with permuted block length will be conducted, using the “Randomization-In-Treatment-Arms” software (RITA, Evident, Germany). The application of neo-adjuvant chemotherapy (neo-adjuvant vs. no neo-adjuvant treatment) will be the stratification factor.

In the present study, participants will be kept blind to the research question, as much as possible. They will be informed that two exercise interventions (HIIT vs. myofascial release training) will be compared, in terms of their effect on cognitive performance, blood parameters and common cancer related side effects, in patients with breast cancer. Accordingly, patients will not know the specific hypotheses of the trial. They will not know if they are allocated to the experimental or to the control group.

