### Primary endpoint

The primary endpoint of the present study will be the change of test-scores from baseline (t_0_) to after completion of the exercise intervention (t_1_), in the test battery recommended by the International Cancer and Cognition Task Force (ICCTF) to capture CRCI [59]. The ICCTF test battery comprises of the Hopkins Verbal Learning Test – Revised (HVLT-R), Trail-Making-Test A/B (TMT-A/TMT-B) and the Controlled Oral Word Association Test (COWAT).The HVLT-RThe HVLT-R was developed to measure forgetfulness in the domain of verbal memory in individuals at the age of 16 and older [67]. The test includes a list of 12 nouns, which will be read to the participants. Then, the participants will be instructed to repeat as many words from that list as they can remember in any order. This process will be repeated three times. The sum of correct recalled words at all 3 learning trials (“Total-Recall”) has been described as measure of learning efficiency and short-term verbal memory [68] and will be used for analyses. The HVLT-R offers six parallel forms. As recommended for repeated testing, the parallel forms 1, 2 and 4 will be used at t_0_, t_1_ and t_2_ [68]. The order of test forms at the 3 measurement time points will be random but counterbalanced across participants. The HVLT-R shows adequate psychometric properties [69, 70].TMT-A/BThe TMT-A will instruct participants to connect randomly distributed numbers from 1 to 25 as quickly and as correctly as possible, in ascending order. The time participants require for completing TMT part A has been described as a valid measure of selective attention [71] and will be used for analyses in the planned study. TMT-B will instruct participants to connect randomly distributed numbers (1 to 13) and letters (A to L) in ascending order, alternating between numbers and letters as quickly and as correctly as possible. The time participants require for completing TMT part B has been reported as valid measure of executive functioning subdomain set-shifting [71] and will be used for analyses. In the present study, the Langensteinbacher version of the TMT (TMT-L) [72] will be applied. It will be operated via the Wiener Test-System (WTS) (Schuhfried, Vienna, Austria) and adequate psychometric properties have been reported for it [72]. TMT-L parallel versions S1, S2 and S3 will be used in a random order at the 3 measurement time-points, but counterbalanced across participants.COWATThe German version of the COWAT will be used in the present study [73]. Participants will be instructed to name as many words as possible in one min, beginning with a given letter. As recommended in the German test-manual [73], the letters S, P and M will be used at the 3 measurement time points. The order of the letters will be random, but counterbalanced across participants. The number of words participants will produce will be used for analyzation. Adequate psychometric properties for the German version of the COWAT have been reported [73].

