### Sample size calculation

Sample size calculation was done to investigate the effect of exercise-intervention on the primary endpoint (objectively assessed cognitive performance using test battery of the ICCTF), in an analysis of covariance model (ANCOVA) using G*Power 3.1.9.2 software [87]. It was hypothesized that the changes in the test scores in the ICCTF test-battery, from baseline to after completion of the exercise-intervention, differ significantly between the HIIT group and the PCG-training group. Previous studies have shown that regular, low to moderate, exercise exerts rather small beneficial effects on CRCI in breast cancer patients [44–48]. However, pronounced effects of HIIT on fitness, cardiovascular health, fatigue and biomarkers have been reported in cancer patients [55–58]. Changes in these factors are discussed to play a pivotal role in the genesis of CRCI [24]. In accordance with it, we expect more meaningful effects of HIIT on CRCI compared to low to moderate exercise interventions. A medium effect of d = .5 was defined for sample size calculation. Alpha was set at 5%, but Bonferroni corrected due to multiple testing (4 outcome variables), leading to an adjusted alpha of 1.25%. Test power (1-β) was set at 80%. Participants’ test scores at baseline are included as covariate in the model. Required sample size in such an ANCOVA model can be calculated as (1-ρ^2^)*n, with ρ representing the correlation between participants’ baseline and post-treatment outcome-scores and n representing the sample size that would have been required, if a t-test of post-treatment outcome-scores was applied [88]. The correlation between patients’ test scores at baseline and at t_1_ was estimated with ρ = .6. This estimation was based on preliminary results (*N* = 40) of an ongoing trial of our group [89], indicating correlations between baseline and post-intervention measures of the applied tests of .6 and .8. Under the presuppositions made, the sample size calculation showed that 59 patients would be required in each group (*N* = 118). Based on attrition rate reported in existing studies applying HIIT in breast cancer patients during chemotherapy [49, 51] we accounted for 15% drop-out rate, leading to a total sample size of *N* = 136 patients.

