### Statistical analysis

An intention to treat (ITT) analysis will be performed We will also assess the effect of the complete treatment in a per protocol analysis. Separate 2 × 3 mixed ANCOVAs will be conducted to determine the effects of between-subjects factor exercise-intervention, within-subjects factor measurement time-point and their interaction on primary and secondary outcomes. Patients’ baseline scores of each specific parameter will be used as covariate. A significant main effect, of within-subjects factor measurement time-point, will be further investigated through Bonferroni corrected post hoc pairwise comparisons. Simple effects analyses will be conducted to determine potential group differences at each measurement time-point.

ANCOVA assumptions will be explored. In case of violations of normality assumption, appropriate nonparametric procedures will be used. In case of violations of ANCOVA assumptions of homogenous variances or sphericity, F-test will be adjusted. Eta-square values will be reported as effect size estimates for explained variance, and Cohen’s d values will be reported for post hoc pairwise comparisons.

In addition, an exploratory regression-based mediation analysis will be performed for each intervention induced change in biomarker expression. It will be tested if the change in biomarker expression, from baseline to completion of the exercise intervention, partially mediates the effect of the exercise intervention on the change in cognitive performance. The indirect effect, as combined effect of intervention induced change in biomarker and change in biomarker induced change in cognitive performance (i.e. the effect of mediation), will be calculated (product of regression coefficients). The 95% confidence intervals will be created around the indirect effect using bootstrapping [90, 91].

Statistical analysis will be performed by a statistician blinded to treatment groups. Statistical analyses will be conducted using SPSS 25® (IBM®, Armonk, NY, USA). For mediation analyses, the PROCESS custom dialog box (version 3.1, Model 4) for SPSS [91] will be used. A result will be considered significant at *p*-value equal to or less than .5 (in case of primary endpoint this will be adjusted to .0125).

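### Randomisation is stratified by neo-adjuvant treatment, but the stated ANCOVA adjusts only for baseline; adding the stratum costs one degree of freedom and may recover a little power.

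*Protocol article*

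**What the plan says.** **Randomisation.** Under Randomization and blinding: "A stratified block randomization with permuted block length will be conducted". The next sentence but one reads "The application of neo-adjuvant chemotherapy (neo-adjuvant vs. no neo-adjuvant treatment) will be the stratification factor" (the sentence between them is the end of the software description).

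**Model.** Under Statistical analysis, each outcome gets its own 2 × 3 mixed ANCOVA for the "effects of between-subjects factor exercise-intervention, within-subjects factor measurement time-point and their interaction on primary and secondary outcomes". The patients' "baseline scores of each specific parameter will be used as covariate". No other term is named.

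**Sample size.** The calculation uses the same model with baseline as the only covariate. Alpha of 5% is "Bonferroni corrected due to multiple testing (4 outcome variables), leading to an adjusted alpha of 1.25" per cent. Power is 80%, d = .5, ρ = .6, giving 59 per group.

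**Test forms.** Under Primary endpoint, alternate material is rotated over visits. For the HVLT-R: "The order of test forms at the 3 measurement time points will be random but counterbalanced across participants". For the TMT: "TMT-L parallel versions S1, S2 and S3 will be used in a random order at the 3 measurement time-points, but counterbalanced across participants". For the COWAT: "The order of the letters will be random, but counterbalanced across participants". Balance within each arm is not stated, and form, version or letter is not a model term.

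**The concern.** Stratified permuted blocks keep the arms nearly equal within each stratum, so a difference in outcome between strata hardly moves the treatment estimate. A model without the stratum does not know this. It leaves the between-stratum variance in the residual and computes the standard error as if that variance could have fallen unevenly between arms. The test then rejects less often than its nominal level, and power is lost.

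The primary tests run at 1.25% with about 80% power on the planning assumptions, so a precision gain that needs no extra patients is worth taking. It should be fixed before unblinding, because a covariate added later can look data-driven.

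**Working it through.** **Inputs from the protocol article (Sample size calculation).** d = .5; alpha .05/4 = .0125; power .80; ρ = .6; 59 per group. Sidedness is not stated; two-sided is the reading that reproduces the figure.

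**Step 1: reproduce 59 per group.** A two-sided two-sample t-test (noncentral t) at .0125 with d = .5 and 80% power needs 91 per arm. The article's ANCOVA factor is 1 − ρ² = 1 − .36 = .64. Then 91 × .64 = 58.24, rounded up to 59. One-sided .0125 gives 50 and two-sided .05 gives 41, so neither matches. The stated N rests on the baseline-only model and does not depend on the stratum.

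**Step 2: power with the stratum in the model.** The documents do not say how much the stratum predicts. Let it explain a share R² of the variance left after baseline (assumed). The adjusted residual SD is √(.64 × (1 − R²)), and the noncentrality is .5 / (SD × √(2/59)). For R² = 0 this is .5 / (.8 × .1841) = 3.39. The baseline-only standard error exceeds the adjusted one by the factor 1/√(1 − R²). The n per arm for 80% power is 91 × .64 × (1 − R²), rounded up.

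| R² (assumed) | Power, 59 per arm | Baseline-only SE larger by | n per arm for 80% |
|---|---|---|---|
| 0 | 80.3% | 0% | 59 |
| 2% | 81.2% | 1.0% | 58 |
| 5% | 82.6% | 2.6% | 56 |
| 10% | 84.9% | 5.4% | 53 |

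The power column uses 115 residual degrees of freedom; the stratum takes one of them.

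**Step 3: check by simulation that the standard error is too large.** N = 118, permuted blocks within stratum, half the patients neo-adjuvant (assumed), and a stratum difference added on top of the .64 residual variance. In this set-up the adjusted model sits near 80% and the unadjusted one falls below it; Step 2 instead holds .64 as the total. A difference of δ residual SDs between two equal strata adds δ²/4 to the residual variance. For δ = .5 that is .0625, a share of .0625/1.0625 = 5.9%.

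| Stratum difference (residual SD) | Power without → with stratum | Type I error without stratum (nominal .0125) |
|---|---|---|
| 0.3 | 80.0% → 81.1% | .012 |
| 0.5 | 77.6% → 80.3% | .009 |
| 0.8 | 72.6% → 78.6% | .008 |

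At 0.5 SD with no treatment effect, the unadjusted model reports a mean standard error of .152 against an actual sampling SD of .148; with the stratum both are .148. With 4,000 null runs the simulation error on type I error is about √(.0125 × .9875/4000) = .0018. The fall is therefore seen at 0.5 and 0.8 SD but not at 0.3.

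**Step 4: do forms behave the same way?** Same simulation, no stratum effect, form order counterbalanced over all participants but not within arm, equally spaced form effects (assumed).

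| Form effects (residual SD) | Mean model SE | Actual SD | Power without → with form terms |
|---|---|---|---|
| ±0.25 | .153 | .155 | 76.1% → 78.3% |
| ±0.5 | .169 | .168 | 64.7% → 78.4% |

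The model standard error matches the actual one. Leaving forms out costs precision if they differ in difficulty, but the standard error stays valid. With neither stratum nor form effects, adding all the terms gains nothing (81.1% without, 79.9% with).

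**The case against.** **The gain is small and conditional.** Nothing in the documents says that neo-adjuvant status predicts cognition beyond the baseline score. At 2 to 5% of residual variance, adjustment moves power from 80% to 81–83%. The planning correlation is also the lower of the two values reported from preliminary data (.6 and .8); at N = 118, ρ = .7 would give about 89% and ρ = .8 about 98%. This stands, and it limits the point to an inexpensive improvement.

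**The detail may be in a document not shown.** The article does not say that baseline is the sole covariate, and nuisance terms are often left to an analysis plan. This stands in part. But the article names its model terms and sizes the trial on the same baseline-only model, so for the stratum it makes a choice that can be reviewed.

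**A reader might infer that omitting forms and letters also leaves standard errors too large.** The documents do not support that. Form order is counterbalanced across participants and not stated to be balanced within arm, so the standard error is valid (Step 4).

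**A reader might also infer that form differences pull the planned power below 80%.** If forms add variance s² to the within-form score variance, the residual variance is (1 + s²) − (.6 − s²/2)²/(1 + s²). That is .679, .735 or .825 for s² = 2, 5 or 10%, and power would be about 78, 74 or 67%. But this treats ρ = .6 as free of form variance. The article took it from observed scores in preliminary data (N = 40) and does not say whether forms were rotated there. If they were, form variance is already in ρ, and adjustment would be a bonus, not a repair. No document gives a difficulty difference between forms.

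**Conclusion.** The point holds for the stratum. The trial randomises within neo-adjuvant strata and states a model without them. If the stratum is prognostic beyond baseline, the standard error is somewhat too large and the test conservative. Across an assumed 0 to 10% of residual variance, power with adjustment at 59 per arm runs from about 80% to 85%. These figures rest on the article's d, ρ and alpha read as two-sided, and on a single-visit ANCOVA of t1 on baseline as in the sample size section, not on the full 2 × 3 model.

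It would be wrong to conclude that the treatment estimate is biased, that false positives increase, or that 59 per group is invalid; none of these follows. Test forms, versions and letters are a separate and optional precision question whose size the documents cannot settle.

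**What to change.** Add the neo-adjuvant stratum, as recorded at randomisation, as a fixed between-subject factor in every primary and secondary model. It enters the stated mixed ANCOVA directly as a main effect. The cost is one sentence and one of about 115 residual degrees of freedom. The variable must already be known at randomisation, and planned therapy is captured at enrolment.

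Optionally, for HVLT-R, TMT-A/B and COWAT, also adjust the baseline-to-t1 comparison for the form, version or letter used at t0 and t1. This costs up to four more degrees of freedom and requires the form given to be recorded for each visit. Form at the analysed visit changes over time, so it does not fit the 2 × 3 mixed ANCOVA as an ordinary between-subject term; it belongs in a t1 model or a mixed model with time-varying terms. If either adjustment is left out, say why, and settle the choice before unblinding.

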### Groups and interventions

Patients will be allocated either into a HIIT or a placebo control group. High-intensity interval endurance training and placebo control group will be conducted at the Clinic Northwest in Frankfurt (Germany), simultaneously with the patients’ first-line chemotherapy regimen, typically lasting 12 to 18 weeks.HIIT GroupPatients will receive a supervised HIIT on a stationary bicycle ergometer (Ergoselect 100 Typ K, Ergoline, Bitz, Germany). Sessions will be carried out 3 times per week with at least 24 h rest between sessions. The first 5 min (min) of each training session will be warm-up at low-intensity (cadence at 60–70 rpm (rpm) and wattage according to 57–63% of patient’s maximum heart rate (HR_max_)). During the first 8 weeks of patients’ chemotherapy, HIIT will consist of 3 × 3 min high-intensive intervals (cadence at 80–100 rpm and wattage according to 85–90% of HR_max_) interspersed by 90 s active rest-intervals (cadence at 60–70 rpm and wattage according to 57–63% of HR_max_). During the second half of patients’ chemotherapy, the number of intervals will be increased to 5 [49]. The last 5 min of each training session will be cool-down at low-intensity (cadence at 60–70 rpm and wattage according to 57–63% of HR_max_). Accordingly, duration of each HIIT session will be approximately 20–25 min during the first 8 weeks of patients’ chemotherapy and 30–35 min during the second half of patients’ chemotherapy. In cases of participants showing blunted heart rate response to exercise, (i.e. resulting from medications like beta-blocker medication) ratings of perceived exertion on the Borg scale [60] will be used to control exercise intensity rather than heart rate [61]. In such cases, warm up, cool down and active rest intervals, interspersed between high-intensive intervals, will be conducted at wattage in accordance with a rating of perceived exertion of 10–12 on the Borg scale. High-intensive intervals, in such cases, will be conducted at wattage in accordance with a rating of perceived exertion of 16–18 on the Borg scale. Any deviations from the protocol will be recorded. High-intensity interval endurance training will be conducted in addition to the standard medical treatment and physiotherapy.Placebo Control Group (PCG)Patients allocated to the PCG will receive a supervised myofascial release training 3 times per week with at least 24 h rest between sessions. The training sessions consist of seven standardized exercises using a foam roll (Blackroll, Bottighofen, Swiss): self-massage of the soles of the feet (standing on one leg), of the calves (lying in dorsal position), of the hamstrings (lying in dorsal position), of the thighs (manually while lying in dorsal position), of the neck (lying in dorsal position), of the lower and upper back (leaning backwards against a wall in standing position), as well as self-massage of the upper arm and shoulder (leaning sideways against a wall in standing position). During the first 8 weeks of patients’ chemotherapy, each exercise will be repeated 6 times on each side of the body. During the second half of patients’ chemotherapy, each exercise will be repeated 10 times on each side of the body. Between each exercise, participants will do low-intense shoulder and hip mobilization exercises for 2 min. Accordingly, duration of each PCG session will be approximately 20–25 min during the first 8 weeks of patients’ chemotherapy and 30–35 min during the second half of patients’ chemotherapy. Any deviations to this protocol will be recorded. Myofascial release training will also be conducted in addition to the standard medical treatment and physiotherapy.

PCG-training was designed as attention control condition. Both treatments, HIIT and PCG-training, will be carried out individually and will be supervised by independent sport-therapists. Training frequency and duration of HIIT and PCG training sessions will be equal, to ensure that the attention, the treatment contact and the nonspecific therapist effects are balanced between HIIT group and PCG. However, PCG-training (myofascial release training), unlike the HIIT, will induce hardly any muscular effort and cardiovascular stimulation [62].

Exercise-treatments will be carried out neither on chemotherapy days, nor 24 h after a chemotherapy application [63]. Other contraindications that prohibit participation in a training session of HIIT or PCG are described below:InfectionsHemoglobin < 8 g per deciliterPlatelet counts < 10,000/μlFeverNauseaDizziness

Patients’ compliance to the exercise program will be strengthened by the individual supervision patients receive. Each patient will have one sport-therapist that will run all the training sessions. The sport-therapist will monitor the patient’s exercise sessions closely and will motivate the patient to apply the protocol. The sport-therapist will provide feedback on patients’ progress and will discuss benefits and barriers of the exercise with the patient. Feedback and support from sport-therapists have been reported to promote adherence to exercise programs in breast cancer patients [64, 65]. To further increase adherence to the training, participants will receive an E-mail every Friday afternoon by their sport-therapist summarizing their previous workout and reinforcing patients’ adherence by praising their attendance and discipline in the program. The E-mail will also contain the training schedule for the following week with the days and times of the planned training sessions.

### Data collection and timeline

Data will be collected during the process of enrollment (−t_0_), at baseline (t_0_), after completion of the exercise intervention (equivalent to the end of patients’ first-line chemotherapy) (t_1_) and 6 months after completion of the exercise intervention (follow-up, t_2_). During the enrolment process, the patients’ medical record and planned therapy, demographic (age, sex, education) and anthropometric data (weight, height, Body Mass Index), as well as past medical history and current medication will be captured. Baseline measurement will be conducted shortly after diagnosis and 1–3 days before beginning of patients’ medical treatment. At t_0_, primary outcome measures and all secondary outcome measures of the study (see “Primary endpoint” and “Secondary endpoints” section below), will be captured. Following the intervention period, i.e. the end of first-line chemotherapy (t_1_), and 6 months after that (t_2_), the primary outcome measures and all the secondary outcome measures will be re-assessed. The detailed study schedule is provided in Fig 2. The “Standard Protocol Items: Recommendations for Interventional Trials” (SPIRIT) checklist [66] is provided as an additional file 2 to this publication.

